Before the training (T0), a battery of neurocognitive tests from the Developmental NEuroPSYchological Assessment, 2nd edition (NEPSY-II [49, 50];) spanning different domains, and, specifically, social perception abilities, is administered to all participants. Both groups also receive a 10-min training of how to move within the GRAIL environment using a custom-made navigational application. Then, a pre-training evaluation through a VR game session, based on the same paradigm of the VR experimental training but in a different scenario, and a computer-based Action Prediction task [51] are administered. Moreover, at T0, both patients and parents compile questionnaires on quality of life (Tno-Azl (Netherlands Organisation for Applied Scientific Research Academic Medical Centre) Children’s Quality Of Life questionnaire (TACQOL), TNO Quality of life/LUMC, 2001 [52];) and parents also complete the Child Behaviour Check List (CBCL [53, 54];).

Performance at the VR tasks is monitored for all the sessions of the training period (T1). In order to verify and compare the effects of the experimental and control training sessions, at the end of the 2-week training (T2) all participants are re-evaluated with the same neurocognitive tests, the VR evaluation scenario and the Action Prediction task.

With the aim to investigate the far transferability of the effects, a follow-up evaluation is provided after 2 months (T3) with the same protocol used at T0 except for the GRAIL evaluation scenario. Details of the study design are set out in Fig. 1 according to the Standard Protocol Items: Recommendations for Interventional Trials (SPIRIT) Statement [55, 56] (see also Additional file 1).

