### Statistical methods

Demographic, clinical and neuropsychological variables of the two groups of patients are inspected through descriptive statistics. A *t* test and *χ*^2^ are used to assess the differences between the experimental and control training groups at baseline for continuous and categorical variables, respectively, thus allowing us to verify successful randomisation. For each outcome measure, we calculate the change between T0 and T2 (training effect delta) and between T0 and T3 (follow-up effect). Delta is calculated as the arithmetic difference between the second/third time points and the first time point. The delta values of the two groups for the primary outcome measure are compared using independent sample *t* tests (two-tailed). For the primary outcome measure, a Bonferroni correction procedure will be used to control for multiple comparisons. Multivariate analysis of variance will be used to explore differential effects of the trainings in the secondary outcome measures. As to what concerns missing data, a modified intention-to-treat analysis approach will be adopted, including in the analyses all the participants who had completed the pre- and post-treatment evaluation sessions, even if they had not completed all the training sessions. No imputation of missing data, however, will be used considering the limited sample size and observation points [58, 59]. The stratification factors (i.e. age and FSIQ), will not be considered in the statistical analyses, assuming that the stratification procedure has ensured a balanced distribution across the two groups.

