Previous research has suggested that an intensive, goal-directed treatment could be at least as effective as one administered over a longer time and it could also be more acceptable by patients and their parents [26]. Although our protocol is in line with the state of the art in this field, the short duration and the required hospitalisation may limit the possibility of controlling the efficacy of this intervention on everyday life. Further, the use of expensive technology makes it difficult to replicate and extend the training to a wider sample. Future research may implement the VR-Spirit training using more accessible and wearable devices (e.g. X-Box Kinect and VR head-mounted displays), that allow it to be administered it in more ecological contexts.

The GRAIL technology is a medical device with 93/42EEC certification provided with safety equipment to prevent any risk associated with its use. However, VR treatments could be accompanied by unwanted side effects such as nausea and headache, which are referred to as simulator sickness or cyber sickness [68]. Although previous studies adopting GRAIL demonstrated its acceptability by clinical paediatric samples [40, 69], in case a participant should present cyber sickness symptoms the session will be interrupted until their sickness ends. Any episode of cyber sickness will be recorded by the GRAIL therapist and considered for evaluating the feasibility and acceptability of the intervention.

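### The modified intention-to-treat set is a T0/T2 evaluation-completer set: it drops every randomised patient without T2, even from T3 comparisons for which data exist

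*Protocol article*

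**What the plan says.** All of the rule is in the Statistical methods section of the protocol article.

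- **Label:** "a modified intention-to-treat analysis approach will be adopted".
- **Inclusion:** "including in the analyses all the participants who had completed the pre- and post-treatment evaluation sessions".
- **Incomplete training:** such patients are kept, "even if they had not completed all the training sessions".
- **Missing values:** "No imputation of missing data, however, will be used considering the limited sample size and observation points".
- **Analysis:** differences T2 − T0 and T3 − T0 are formed for each outcome. The groups are compared by t tests for the primary outcome and by multivariate analysis of variance for the secondary ones.

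The visit schedule is set elsewhere. The Evaluation sessions and Outcome measures sections place the pre- and post-training evaluations at T0 and T2. The Design section adds that "a follow-up evaluation is provided after 2 months (T3) with the same protocol used at T0 except for the GRAIL evaluation scenario". The Questionnaires section schedules the TACQOL and CBCL at T0 and T3 only. Under Outcome measures, dropout from the two-week training is counted as a feasibility result, with no expected rate.

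**The concern.** Attending T2 happens after randomisation. A set that requires it no longer compares the groups as randomised, and the intention-to-treat label hides this. A patient who leaves before T2 is seen only in the feasibility count.

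If the reasons for missing T2 are linked to the training or differ between arms, the comparison can be biased. The documents give grounds to consider this. The arms differ in content (80 avatar trials plus one game, against a maze game plus four games). Parents know the allocation. The Discussion also allows that "VR treatments could be accompanied by unwanted side effects such as nausea and headache".

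The second problem needs no assumption about dropout. A single rule covers all analyses, with no exception for follow-up, so attendance at T2 decides who enters the T3 − T0 comparison. For the TACQOL and CBCL, the gate is a visit at which neither questionnaire is scheduled.

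The stated reason, a small sample with few observation points, is a reason not to impute. It does not justify leaving out randomised patients whose data for a given comparison are complete.

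**Working it through.** **1. Who is in, under the rule as written**

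| Data available | T2 − T0 | T3 − T0 |
|---|---|---|
| T0, T2, T3 | in | in |
| T0, T2; training incomplete | in | no T3 value |
| T0, T3; no T2 | no T2 value | **excluded although both values exist** |
| T0 only | out | out |

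The third row is the avoidable data loss. The fourth row is where bias can enter.

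**2. Bias in general form**

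Suppose a fraction f of the VR-Spirit arm lacks T2, and their change would have been g SD worse than that of the rest of the arm. With no loss among controls, the analysed difference exceeds the all-randomised difference by f × g. The protocol gives neither f nor g, so both are assumed.

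| f | g | Excess (SD) | Two-sided rejection at nominal 5% when the all-randomised effect is zero |
|---|---|---|---|
| 10% | 0.5 | 0.05 | 5.3% |
| 10% | 1.0 | 0.10 | 6.1% |
| 20% | 0.5 | 0.10 | 6.0% |
| 20% | 1.0 | 0.20 | 9.2% |

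If the leavers would have done better than those who stay, or if the loss is in the control arm, the sign reverses.

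**3. Example on the protocol's own scale**

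The inputs from Estimation of sample size are 21 per group and a relevant mean change of 0.13 in the Action Prediction beta. Assumed: 3 VR-Spirit patients leave with no gain, the other 18 gain 0.13, and controls do not change.

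- Analysed patients: 0.130.
- All assigned: 18 × 0.13 / 21 = 0.111.
- Ratio: 21/18 = 1.17, an overstatement of 17%. With 1 to 4 leavers, the ratio runs from 21/20 = 1.05 to 21/17 = 1.24.

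**4. Does a repeated-measures model cure this?**

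Not for patients with T0 only. Under missing at random, the model predicts their T2 from the patients in the same arm who attended. In the example T0 carries no information about who leaves, so the prediction is the completer gain. Simulating the example with assumed T0–T2 correlations of 0.5 and 0.7 gave, to within simulation error, 0.13 for completers, 0.13 for the likelihood model and 0.11 for all assigned. Assigning zero change to the leavers returns 0.111, because that is what the example assumes of them.

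**5. Precision**

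Two-tailed t-test power at d = 0.8 and alpha 0.05:

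| Analysed per group | 24 | 22 | 21 | 19 | 17 |
|---|---|---|---|---|---|
| Power | 0.774 | 0.736 | 0.716 | 0.670 | 0.619 |

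The planned 0.80 is not reproduced at 21 per group on the stated inputs. That is a separate matter, and this point does not depend on it.

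**The case against.** **Training dropouts are kept.** A reader might infer that the set contains only those who tolerated the training. The text does not support that. A patient who stops training but attends T2 is analysed in the assigned group, so this is not a per-protocol set. For the same reason, the feasibility count of training dropouts is not a count of missing T2 evaluations. This objection stands in full.

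**Cyber sickness is not shown to cause loss.** It is tempting to read the Discussion as predicting withdrawals. What it says is that "in case a participant should present cyber sickness symptoms the session will be interrupted" until the symptoms pass, which describes a pause. It also cites acceptability in earlier paediatric samples. Both arms use the same platform for the same time. Loss that differs by arm is therefore possible but is not documented.

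**T3 without T2 may be rare.** T2 closes a two-week hospital stay and T3 follows two months later, so few patients may be affected. That limits the size of the loss but does not justify the rule. That a patient without T3 adds nothing to a T3 − T0 difference is true of any change score and is no fault of this plan.

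**There is recruitment headroom.** Six strata of eight give 48 places against a target of 42. If all fill, losing 2 per group leaves 22, with power 0.736 rather than 0.670. The Discussion concedes that strata may not fill, and no dropout allowance is tied to the 48. Headroom protects power but does not remove bias.

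**Replacing the t test is not required.** A mixed model does not remove the bias from T0-only leavers, and the sweet-stands score has no T3 value to borrow from. This also stands, and it is why the fix does not rest on a model.

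**Conclusion.** The point holds in limited form. The set is one of T0/T2 evaluation completers carrying an intention-to-treat label. It omits every randomised patient without T2 from all efficacy analyses. As written, it also bars patients with T0 and T3 data from the follow-up comparison, including two questionnaires not scheduled at T2. Both statements follow from the text alone.

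That the efficacy estimate will be biased does not follow. Bias requires that missing T2 be related to the training or differ by arm, and no dropout rate is given from which to judge it. The 0.130 against 0.111, and the 0.05 to 0.20 SD range, are illustrations on assumed losses. They do not predict size or direction. The changes are worth making because they are specific and cheap, and recruitment was still open when the article was written.

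**What to change.** 1. **Label and report.** Describe the set as participants with T0 and T2 evaluations, and report the number missing T2 and T3 by arm.
2. **Define inclusion per comparison.** The T3 − T0 analyses should take all randomised patients with T0 and T3, whether or not T2 was attended. For the Action Prediction beta and the NEPSY-II scores, which have all three visits, a likelihood-based repeated-measures model is one way to do this without imputing. The TACQOL and CBCL need only the T0/T3 pair.
3. **Add one sensitivity analysis.** For both primary measures, including the sweet-stands score, analyse all randomised patients with a T0 value and assign zero change to those without T2. This is a simple imputation with a strong assumption, so it belongs beside the main analysis and not in its place. It is needed because a missing-at-random model leaves T0-only leavers uncorrected.

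The cost is revised wording, slightly more analysis and an explicit missing-data assumption. No visits, patients or procedures change.

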### Design

The study applies a single-centre, randomised, active-controlled trial design. Patients are allocated to one of two groups undergoing two different rehabilitation programmes through a stratified permuted block randomisation procedure [47]. Age and cognitive level (more recently available Full-scale Intelligent Quotient, FSIQ) are chosen as stratification factors. In particular, we consider two levels for age, corresponding to 7.0–12.9 and ≥ 13.0 years, and three stages for cognitive level consistent with, respectively, absence of intellectual disability (FSIQ > 80), from borderline intellectual functioning to mild intellectual disability (80 ≥ FSIQ ≥ 61) and from mild to moderate intellectual disability (60 ≥ FSIQ ≥ 45) (48). Doing so, six blocks are generated and within each block an estimated number of eight patients should be enrolled to achieve and overcome the established sample size. First, participants are allocated to a block depending on the two stratification variables. Second, patients are assigned to one of the two interventions according to specific permuted sequence. Details of the permuted blocks are reported in Table 1.

**Table 1 Tab1:** Stratified permuted blocks randomisation of the study

		Age	
		7–12.9 years	≥ 13.0 years
FSIQ	46–60	CCSSCCSS	SCSCSCSC
	61–80	SCCSSCCS	SSCCSSCC
	> 80	CSCSCSCS	CSSCCSSC

Legend: *FSIQ* Full-Scale Intelligent Quotient, *S* VR-Spirit training, *C* control training

Group 1 (S) receives the social prediction VR training for 2 weeks (four daily sessions in a week). In each 1-h session, 80 trials of the experimental programme and one of four motor games, selected among the applications available in the GRAIL, are administered; for each weekly session, a different game is administered in random order. Group 2 (C) receives a control VR training of the same duration (2 weeks, four 1-h sessions per week) as the experimental training; the control training involves, for each session, a navigational game and the daily repetition of all the four games from the GRAIL suite that are also presented, one per day, in the experimental session; the social prediction experimental programme is not presented in the control training.

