The study design provides for an active control group that participates in a training in VR, playing games already adopted for motor rehabilitation. On one hand, this approach allows us to verify the specificity of the social prediction training in improving social cognition abilities. On the other, it enables us to investigate the effects of VR interventions on other cognitive abilities indirectly involved in the two trainings. Indeed, intrinsic features of VR systems, such as the natural sense of presence, the movement in attractive scenarios and the delivery of complex, multisensorial feedbacks, could enhance visual-spatial ability and sensorimotor integration [32]. However, since both the experimental and the control trainings engage motor systems, any differential outcome of the VR-Spirit vs. the control training is unlikely to reflect motor symptom improvements. Nevertheless, any change in sensorimotor functions as assessed by NEPSY-II subtests should be considered and controlled when analysing and discussing the outcomes of the study.

The VR-Spirit protocol provides a new kind of interventions for neurorehabilitation of patients with cerebellar malformations. While it fills a gap of rehabilitation on social cognition, it is worth mentioning that this approach could only partially address the rehabilitative needs of children, adolescents and young adults with congenital cerebellar diseases, which should necessarily encompass other interventions focussed on the motor [66] and cognitive deficits typically shown by these patients [61]. However, VR-Spirit is a first step to design future rehabilitative protocols targeted on the different clinical manifestations of CCAS.

The literature has widely documented cerebellar engagement in social cognition tasks in both low-level and high-level processing [15, 67]. Accordingly, we could reasonably assume that VR-Spirit activates the cerebellum along with other cortical areas involved by social inference [20]. Although, we did not directly verify this hypothesis. Future studies should consider adopting neurophysiological measures (e.g*.* electroencephalography) in order to investigate whether and how the cerebellum and other cortical areas are engaged by our paradigm.

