Finally, it is noteworthy that the participants are randomly allocated to the two groups, but the psychologist administering the neuropsychological evaluation, the GRAIL therapist and the parents of the patients are not blinded to the typology of interventions. As what concerns randomisation, the use of stratified randomisation has been issued for introducing biases when baseline features of all participants are not available before assignment [70]; nevertheless, it allows control of the effects of influencing covariates in a small sample size [71]. Moreover, while we reduced as much as possible the strata based on the importance of the clinical variables, the availability of patients for our sample may not consent to fulfilling all the blocks [47]. These methodological issues should be considered and discussed when evaluating and interpreting the results of the protocol. The results on efficacy and feasibility will be published in international peer-reviewed journals. Preliminary data on efficacy and feasibility will be submitted when at least half of the target sample has been recruited. Final efficacy results will be submitted within 6 months after the end of the trial.

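### The primary change-score t test leaves out age and FSIQ because balance is assumed, and uses T0 only by subtraction; it stays valid but gives away power

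*Protocol article*

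**What the plan says.** **Primary test.** Statistical methods forms T2 − T0 and T3 − T0 for each outcome: "Delta is calculated as the arithmetic difference between the second/third time points and the first time point". It then states: "The delta values of the two groups for the primary outcome measure are compared using independent sample" t tests, two-tailed. No covariate is named.

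**Stratification factors.** Under Design, patients are allocated "through a stratified permuted block randomisation procedure". "Age and cognitive level (more recently available Full-scale Intelligent Quotient, FSIQ) are chosen as stratification factors", with two age levels and three FSIQ levels, so six strata: "six blocks are generated and within each block an estimated number of eight patients should be enrolled". Statistical methods then excludes both factors: "The stratification factors (i.e. age and FSIQ), will not be considered in the statistical analyses, assuming that the stratification procedure has ensured" a balanced distribution.

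**Filling of strata.** The Discussion describes the factors as covariates with influence in a small sample, and warns that "the availability of patients for our sample may not consent to fulfilling all the blocks".

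**Sensorimotor change.** The Discussion also says that "any change in sensorimotor functions as assessed by NEPSY-II subtests should be considered and controlled when analysing and discussing the outcomes" of the study.

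**The concern.** The reason given for leaving out age and FSIQ does not support the choice. Stratifying takes the part of the outcome explained by those factors out of the true variability of the group contrast. An analysis that omits them still counts that part as residual noise. So if the factors matter for the analysed quantity, balance is an argument for including them. If they do not matter, including them costs almost nothing.

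The handling of T0 raises a separate efficiency question. Subtracting T0 fixes its slope at 1. Estimating the slope is more precise for any T0–T2 correlation clearly below 1. In a trial of 42 patients with a rare condition, precision that costs only wording is worth having.

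Finally, change in sensorimotor function arises after randomisation and may be altered by the training. If the Discussion's remark were carried into the efficacy model, the group effect would be conditioned on a possible consequence of treatment and could be biased.

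**Working it through.** **Inputs from the protocol article.** 21 per group, d = 0.8 on the between-group difference in T2 − T0, two-tailed t test, alpha 0.05, stated power 0.80 (Estimation of sample size); six strata and the sequences in Table 1 (Design).

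**Inputs assumed.** T0–T2 correlation r from 0.3 to 0.9; equal variances at T0 and T2; share R² of the change variance explained by age and FSIQ from 0 to 30%. The article gives none of these.

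**Step 1: the planned test.** Noncentrality = 0.8 × √(21/2) = 2.592 on 40 df. Two-sided power is 0.716, not the stated 0.80; 26 per group would be needed. That gap is a sample-size matter in its own right and is not caused by omitted covariates. The value 0.716 is the comparator below.

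**Step 2: T0 as a covariate.** With equal variances,

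Var(adjusted) / Var(change score) = (1 − r²) / [2(1 − r)] = (1 + r)/2.

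Noncentrality becomes 2.592 / √[(1 + r)/2] on 39 df.

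| r (assumed) | variance ratio | SE ratio | noncentrality | power |
|---|---|---|---|---|
| planned t test | 1 | 1 | 2.592 | 0.716 |
| 0.3 | 0.65 | 0.81 | 3.215 | 0.880 |
| 0.5 | 0.75 | 0.87 | 2.993 | 0.831 |
| 0.7 | 0.85 | 0.92 | 2.812 | 0.783 |
| 0.9 | 0.95 | 0.97 | 2.660 | 0.737 |

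A simulation with 42 patients, six strata of random size and blocks of four gave 0.71 for the t test and 0.82 with T0 as covariate at r = 0.5, in line with the formula.

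**Step 3: omitted strata and the standard error.** If the strata are balanced and explain a share R² of the change variance, the true SE of the contrast is √(1 − R²) times the one the t test reports. The test then rejects under the null when |t| on the correct scale exceeds 2.021/√(1 − R²). Approximating with t on 40 df:

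| R² of change (assumed) | effective cut-off | type I error |
|---|---|---|
| 0 | 2.021 | 0.050 |
| 5% | 2.074 | 0.045 |
| 10% | 2.130 | 0.039 |
| 20% | 2.260 | 0.029 |
| 30% | 2.416 | 0.020 |

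Simulation agrees. With 18% of the change explained, the reported SE was 0.308 against an empirical 0.283, type I error was 0.031, and power was 0.724 unadjusted against 0.791 with the strata added.

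The condition on the *change* is essential. When age and FSIQ explained 20% of both T0 and T2 equally, their effect cancelled in the difference: SE 0.307 against 0.311, type I error 0.050.

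**Step 4: cost of the strata if they predict nothing.** In simulation, adding them moved power from 0.71 to 0.705 (t test) and from 0.82 to 0.812 (model with T0), about one point at most.

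**Step 5: is balance assured?** At the target of 42, an even fill gives 42/6 = 7 per stratum. Counting the first seven letters of each Table 1 sequence gives S:C of 3:4 in each of the three younger strata and 4:3 in each of the three older ones. That is 9:12 in the younger group and 12:9 in the older. Overall the arms are 21:21, but the tilt lines up with age. It disappears only at 8 per stratum, which is 48 patients.

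**The case against.** The strongest defence is that the analysis is pre-specified, open about what it omits, and valid: under randomisation a change-score comparison is unbiased, and no inflation of type I error arises. That stands. What remains is efficiency and an unsound justification.

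Several stronger readings are tempting, and the document does not support them.

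- *Baseline is ignored.* It is not; T0 enters each delta with slope 1. Only age and FSIQ are excluded on purpose.
- *The standard errors are wrong.* A reader might infer this from the exclusion of the stratification factors. It follows only if those factors predict the change. The article gives no such figure, and calling them influential covariates does not say that they influence change.
- *The test is conservative and the balance is unreliable, both at full strength.* The two pull against each other: the less balance stratification achieves, the less conservative the unadjusted test becomes.
- *Omitting covariates causes the shortfall from 0.80.* It does not; 21 per group falls short of a two-tailed test at d = 0.8 whatever the covariates.
- *The plan adjusts for sensorimotor change.* Statistical methods specifies no such covariate. The remark is loose Discussion wording, worth tightening but not a defined model.

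It is also fair that the gain from T0 shrinks as r rises: only about two points at r = 0.9, and at r near 1 the lost degree of freedom can cancel it.

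**Conclusion.** The point holds as one of efficiency and reasoning, not of validity. Assumed balance does not justify leaving out age and FSIQ, and the balance itself is not assured. Using T0 as a covariate would raise power from about 0.72 to between about 0.74 and 0.88 for r from 0.9 down to 0.3, given equal variances at T0 and T2. The SE problem is conditional: none if age and FSIQ explain none of the change, and type I error of about 0.045, 0.04, 0.03 and 0.02 if they explain 5%, 10%, 20% and 30%. The direction of both effects is well supported; their size rests on correlations and R² values that the article does not give. The change should be made, since it improves a small trial at almost no cost.

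**What to change.** - In Statistical methods, replace the t test for the primary outcome by a linear model of the T2 value on group, T0 value, age stratum (two levels) and FSIQ stratum (three levels), tested two-sided, and report the adjusted mean difference with its 95% CI.
- Use the same model at T3 for the Action Prediction coefficient only, because the VR evaluation is not repeated at T3.
- Delete the sentence that excludes the stratification factors.
- In the Discussion, reword the remark on sensorimotor change so that post-randomisation change is described only and does not enter the efficacy model; if a sensorimotor covariate is wanted, use its T0 value.

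**Cost.** Wording only. The strata are known at randomisation, and the analysis set already requires T0 and T2 evaluations. Residual degrees of freedom fall from 40 to 36 (one for T0, one for age, two for FSIQ). If the strata turn out not to predict the outcome, including them costs about one point of power.
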